### Outcomes {12}

#### Primary outcome

The primary outcome will be fracture healing 12 months after the start of treatment, defined that both, bony consolidation and functional restoration, must be present (composite endpoint):

Bony consolidation is defined as at least three out of four cortices are consolidated based on the radiological findings.

Functional recovery will measured using patient reported outcome measures (PROM) separately for the upper and lower extremity: Disability of Arm, Shoulder and Hand (DASH) score with a minimal clinically important difference (MCID) of 10 points and Lower Extremity Functional Scale (LEFS) with an MCID of 9 points. The primary outcome is met, if either the score will be at least as good as the normative value of the healthy population, depending on age and sex, or if at least an improvement equal to the MCID will be achieved for the respective outcome.

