##### Disability of Arm, Shoulder and Hand (DASH) questionnaire:

The DASH questionnaire, which has been established for over 25 years, will be used to record functional limitations of the entire upper limbs. Its validity has been demonstrated by several studies [22, 23]. It consists of 30 questions, which are answered using a 5-point Likert scales of different characteristics. The maximum score is 100, with low scores indicating a minor limitation. The first part comprises questions on the functional capacity of the upper extremities, while the second part requires answers to questions on symptoms. The questionnaire was developed by the American Academy of Orthopedic Surgeons (AAOS) in collaboration with the Council of Musculoskeletal Specialty Societies (COMSS) and the Institute for Work and Health (Toronto, Canada). For this study, the validated German version is used [24]. To assess whether functional restoration is present, the DASH must show an improvement of at least 10 points compared to baseline or the score must be at least as good as the normative value of the healthy population. A study on normative values in the German population serves as the basis for the normative values [24]. Here, the median values of the non-clinical manual sample are considered normative values, depending on age and sex [24]. The norm values for a manually active sample are taken into account, since these are somewhat higher than those for a non-manually active sample are. It is considered a success for all patients if they have at least as good a value as the norm value of the healthy, manually active sample, regardless of whether they are engaged in manual activity or not.

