##### Lower Extremity Functional Scale (LEFS) questionnaire:

The LEFS is a validated self-assessment questionnaire that records activity restrictions following lower limb injuries and objectively depicts the course of therapy. It consists of 20 questions on various activities, answered using a 5-point Likert scale (“no difficulties”: 4 points to “extreme difficulties”: 0 points). The maximum achievable score is 80, with a higher score indicating better function. In a Dutch study from 2017, a median score of 77 was determined for 1,014 participants, with only slight differences between women and men (median score 76 and 78) [25]. In this study, the validated German version of the questionnaire will be used, for which a high reliability (ICC: 0.98) and consistency (CA: 0.95) was shown [25]. To assess whether functional production is present, the LEFS must either show an improvement of at least 9 points compared to baseline or the score must be at least as good as the normative value of the healthy population. A study by Dingemans et al. on normative values in the Dutch population serves as the basis for the normative values, as there is no study on normative values in the German population. It is assumed that the Dutch normative values are transferable to the German population. The median values of the healthy sample as a function of age and sex are regarded as normative values [24].

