### Participant timeline {13} (Fig. 1)

Seven visits will take place at the respective study center. During the screening visit, the inclusion and exclusion criteria are checked, and the patient is informed about the study. If these criteria are met, consent is obtained and the patient is randomized into one of the two groups. Patients receiving LIPUS treatment are prescribed an ultrasound device. For patients in the surgical group, preparations for the operation are made (e.g. anesthesia information). After the patient has been randomized, 7–21 days may elapse before the ordered ultrasound device arrives at the study site, or before all preparations for surgery have been completed and a date has been set. If more than four weeks elapse between randomization and the start of ultrasound therapy or surgery, the inclusion and exclusion criteria must be checked again at the baseline visit for possible changes. Repeated imaging is at the discretion of the attending physician and is performed independently of the study.

At the baseline visit (day 0), patients in the intervention group will receive the ultrasound device and will be instructed on the use. In addition, the site of the non-union to be treated by ultrasound will be marked. Before the start of LIPUS treatment or surgery, baseline data will be collected (Fig. 2) and a physical examination will be performed. In both treatment groups, NRS will be used to evaluate the patients’ pain, and questionnaires will be used to assess the general quality of life (SF-12) and the function of the affected limb (DASH or LEFS).

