## Statistical methods

### Statistical methods for primary and secondary outcomes {20a}

Treatment with LIPUS will be analyzed with a non-inferiority test against surgical treatment for the primary endpoint of fracture healing. A one-sided 97.5% confidence interval will be estimated for the difference in the proportion of fracture healing between the two groups. If the lower limit of the confidence interval will be greater than the non-inferiority limit of −25 percentage points, the null hypothesis of no non-inferiority will be rejected at the significance level α = 0.025. In addition, a generalized linear mixed model (GLMM) will be fitted to evaluate the robustness of the result for the binary endpoint of fracture healing. Treatment, sex, age and upper vs. lower limb will be considered as fixed effects. The study sites will be modeled as random effects. In order to estimate the risk difference for the treatment in the GLMM, the identity link will be considered as a link function for this endpoint. In addition, the analyses will be performed separately for radiographic bony consolidation and functional restoration. An intention-to-treat (ITT) analysis will be performed as well as a per-protocol (PP) analysis as a sensitivity analysis. The safety analysis will be based on the documented (S)AEs/(S)ADEs. All secondary endpoints will be analyzed exploratively, that is, without adjustment for multiple testing, using standard methods of statistical inference appropriate for the scale level of the endpoint in question. Scores for DASH and LEFS will be considered as continuous outcomes for which linear mixed regression models will be used, where sex, age, and upper or lower extremity will be included as fixed and study sites as random effects.

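### The DASH and LEFS models list an extremity term that is constant within each scale, do not name treatment, and leave out the baseline score

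*Protocol article*

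**What the plan says.** The section on statistical methods for primary and secondary outcomes {20a} fixes the model class for the functional scores: "Scores for DASH and LEFS will be considered as continuous outcomes for which linear mixed regression models will be used". The same sentence gives the terms: "where sex, age, and upper or lower extremity will be included as fixed and study sites as random effects".

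Earlier in that section, the generalized linear mixed model (GLMM) that checks the primary endpoint has the same adjustment terms and also random site effects, but there the arm is named: "Treatment, sex, age and upper vs. lower limb will be considered as fixed effects".

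Other sections tie each questionnaire to one limb. Under Primary outcome, function is "measured using patient reported outcome measures (PROM) separately for the upper and lower extremity". Under Participant timeline {13}, questionnaires at the baseline visit assess quality of life and "the function of the affected limb (DASH or LEFS" as applicable. The scales differ in direction and range. For DASH: "The maximum score is 100, with low scores indicating a minor limitation". For LEFS: "The maximum achievable score is 80, with a higher score indicating better function".

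The baseline score already has a role in the functional success rule: "the DASH must show an improvement of at least 10 points compared to baseline", unless the norm value is reached. LEFS has the same kind of rule with 9 points.

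All secondary endpoints are declared exploratory. The section on non-adherence and missing data {20c} leaves further detail on all endpoints to the statistical analysis plan.

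**The concern.** The covariate list matches that of the healing model, where upper and lower limb patients are analysed together and extremity varies. It does not carry over to scores that exist for only one limb each. Read as written, the list contains a term that can do nothing in a DASH model or a LEFS model. It does not name the term of interest, and it omits the baseline score, usually a strong predictor of a later score on the same questionnaire.

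DASH and LEFS are the instruments behind the functional half of the composite endpoint, and their continuous analysis is where a reader will see how large any functional difference is. Each scale uses only part of the 370 patients, so precision is worth having. The extremity term also leaves a doubt: someone writing the analysis plan from this sentence could ask whether the two scores are meant to share one model.

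**Working it through.** The article gives no figure for this analysis, so there is none to reproduce. The check compares the stated terms and then works out what each defect does.

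**1. Terms side by side (Statistical methods {20a})**

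| Term | GLMM for healing | DASH/LEFS models |
|---|---|---|
| Treatment | listed | not listed |
| Sex, age | listed | listed |
| Extremity | listed | listed |
| Site (random) | listed | listed |
| Baseline score | not applicable | not listed |

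**2. Extremity within one scale.** In a DASH analysis every patient is an upper limb patient, so the extremity column is a multiple of the intercept. The listed fixed effects with an intercept (intercept, sex, age, extremity) form a matrix of 4 columns and rank 3. Replacing extremity by treatment gives 4 columns and rank 4, so the treatment effect can be estimated. LEFS is the mirror case.

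**3. Pooling, the only way extremity could vary.** Assume a benefit of one minimal clinically important difference on each scale: −10 points on DASH (low is good) and +9 on LEFS (high is good). With a share p of upper limb patients and arms balanced within limb, a common treatment coefficient on raw scores is about

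−10p + 9(1 − p) = 9 − 19p.

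- p = 0.3: 9 − 5.7 = +3.3
- p = 0.5: 9 − 9.5 = −0.5
- p = 0.7: 9 − 13.3 = −4.3

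The same clinical benefit changes sign with the limb mix. A simulation of 2,000 trials of 370 patients agrees (assumed: equal limb split, SDs 20 and 16, correlation 0.5, no site effect): the pooled coefficient averaged −0.53. The limb mix is not given in the article, so p is an assumption; the conflict of direction does not depend on it.

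**4. Baseline score.** With baseline-outcome correlation r (assumed), adjustment multiplies the residual variance by 1 − r² and the standard error by √(1 − r²). The equivalent gain in sample size is 1/(1 − r²).

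| r | Residual variance | Standard error | Equivalent sample size |
|---|---|---|---|
| 0.3 | 0.91 (−9%) | × 0.95 | × 1.10 |
| 0.5 | 0.75 (−25%) | × 0.87 | × 1.33 |
| 0.7 | 0.51 (−49%) | × 0.71 | × 1.96 |

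In the same simulation a DASH-only model with treatment recovered the assumed −10 both without baseline (mean −9.99, SD of the estimate 2.87) and with it (mean −9.96, SD 2.50). The ratio 2.50/2.87 = 0.87 matches the table. The omission therefore costs precision and causes no bias.

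**5. Reach.** The stated 166 per group rests on healing proportions alone:

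(1.960 + 1.282)² × (0.86 × 0.14 + 0.75 × 0.25) / (0.25 − 0.11)² = 10.51 × 0.3079 / 0.0196 ≈ 165.1, rounded up to 166.

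No DASH or LEFS model enters it. The primary confidence interval is likewise for a difference in healing proportions.

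**The case against.** The strongest reply is that the sentence is a shortened list of adjustment terms. It does not say that only these terms enter, the trial exists to compare two arms, and the healing model in the same section names treatment. Nobody would fit the model without the arm. An aliased extremity column is dropped by the software and leaves every other coefficient unchanged. Baseline adjustment is a choice about precision, further detail is deferred to an analysis plan that is not shown, and the analyses are exploratory.

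Most of this stands, and it limits the point. Three stronger readings are tempting and are not supported:

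- A reader might infer that the model cannot estimate the treatment effect. That follows only if the list is taken as complete. The healing model makes a drafting slip far more likely, and the redundant term alone would not block estimation.
- A reader might infer that raw DASH and LEFS scores will be pooled. Nothing says so. Function is measured separately by limb, and the sentence speaks of models in the plural.
- A reader might infer that repeated scores from one patient will be treated as independent, giving standard errors that are too small. Questionnaires are given at several visits, but nothing says that several visits enter one model, and no visit term is listed. With one score per patient, a site effect alone is coherent.

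The reply does not remove the defect. The article names the model class, the fixed effects and the random effect rather than deferring them, and the named list does not suit these scales. An analysis plan that follows it inherits a redundant term; one that corrects it departs from the published text.

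**Conclusion.** The DASH/LEFS model is mis-specified as stated, with minor to moderate consequences. Two facts rest on the text alone: extremity is constant within each scale, and treatment is not named although the parallel model names it. The third part, the absent baseline score, is a loss of precision. Its size (9%, 25% or 49% of residual variance) depends wholly on assumed correlations of 0.3, 0.5 or 0.7, because the article gives none.

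The pooled-score calculation shows why pooling is no way to make the extremity term meaningful; it does not describe the planned analysis. A reader might also extend the point to the primary result, since the same questionnaires define functional recovery. The article does not support that: the primary non-inferiority test and the sample size use healing proportions, and functional restoration is also to be analysed separately by the methods of the primary endpoint.

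**What to change.** Replace the model sentence with wording to this effect:

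> DASH and LEFS scores will be analysed in separate linear mixed models, with treatment, the baseline score of the respective scale, age and sex as fixed effects and study site as a random effect.

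Delete the extremity term. Separate models already account for limb, which is also a stratification factor, because each holds only one limb. If several visits are to enter one model, add visit, treatment-by-visit and a patient random effect; otherwise state the visit analysed, and leave those terms out.

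The cost is one or two sentences in the protocol or the analysis plan. Every variable is already collected, and neither the visit schedule nor the sample size changes.

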### Interim analyses {21b}

Interim analyses will only be conducted for the purpose of evaluating safety data and making possible recommendations for adjusting the risk–benefit assessment. If serious deviations from the protocol should be identified, the study will be prematurely terminated at the respective study site. The principal investigator of the study will have the right to terminate the entire study for ethical, clinical, or administrative reasons or the responsible ethics committee may recommend it, the scientific/ethical review committee accompanying/supervising the study, or a state monitoring institution. If new findings and/or risks come to light that necessitate a new risk–benefit assessment and the outcome is unfavorable, this will be a reason for terminating the entire study. The termination of the study would be communicated to the responsible ethics committees. If the study is terminated prematurely, all investigators and participating patients will be informed. The investigators at the study site will also ensure that appropriate further treatment and follow-up will be organized for the recruited patients. A follow-up appointment will be arranged for all patients within 14 days. If further follow-up care is required, this will be organized accordingly by the investigators of the study site.

### Methods for additional analyses (e.g., subgroup analyses) {20b}

Subgroup analyses will be performed separately for upper and lower extremities, age (≤ 60 vs. > 60 years) as well as for sex.

### Methods in analysis to handle protocol non-adherence and any statistical methods to handle missing data {20c}

At visit three, approximately 120 days after start of the intervention, it will be established whether the treatment has been successful. If the treatment is classified as unsuccessful for patients, the corresponding patients from both treatment groups will be offered alternative or further treatments, including (renewed) surgery. Should such additional interventions occur after visit 3, the data from visits 4 and 5 should only be viewed with caution. If analyzed according to the ITT principle, positive treatment effects of the surgical intervention could overestimate the effect of the LIPUS treatment. If patients with additional surgical intervention are counted as surgically treated, the effect of LIPUS treatment could also be overestimated, as the patients who failed and therefore underwent surgery are no longer considered in this group. If all patients with an additional procedure were excluded from the analysis, the treatment effects in both groups could be overestimated, as these patients with a failure are no longer included. For the analysis of the primary endpoint, all patients who will receive an additional surgical intervention are therefore classified as failures, as it can be assumed that the intervention was performed due to a lack of success. For the evaluation of the secondary endpoints, the last observed values before an additional surgical intervention will be carried forward (last observation carried forward (LOCF)). Because of the different interventions (non-recurring surgery vs. daily treatment with LIPUS), a smaller compliance rate in the LIPUS group will be expected, resulting in presumably lower success rates. To account for these compliance differences in the application of the treatments, the ITT population will be regarded for primary analyses. In order to estimate the differences of the treatments when applied correctly, the PP population will be analyzed additionally.

If less than 5% of the values of the primary endpoint are missing, the primary analysis will be performed on the complete data available and a sensitivity analysis will be performed using LOCF. If at least 5% of the values are missing, the primary analysis will be performed on the basis of multiple imputation using the MAR (missing at random) assumption. The analysis on the complete data will be performed as a sensitivity analysis. Further details on the planned analyses of all endpoints and on how to deal with missing values will be defined in the statistical analysis plan.

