### Criteria for discontinuing or modifying allocated interventions {11b}

Study participation can be terminated upon the patient’s request, and patients may withdraw from the study for any reason at any time. Investigators may discontinue a patient’s study participation in case of health deterioration, non-compliance, intake of non-permitted medication or if an inclusion or exclusion criterion was violated after study inclusion.

For both groups, after 42 and 120 days of the respective intervention, routine imaging (X-ray or computed tomography, performed independently of the study) will be used to evaluate whether there are any signs of dynamic bone healing. If there are no signs of bone healing at all after 120 days, compared to the initial findings, these circumstances will be discussed with the patient and alternative treatment methods, including a new surgical revision, will be offered. In addition, a wait-and-see approach will be possible at this point. Routine imaging will also be performed after 200 days to confirm that at least three out of four cortices are consolidated. If the non-union is found to be healed after 200 days, no further imaging will be performed unless this is deemed necessary at the doctor's discretion at the end of the study at day 365.

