### Relevant concomitant care permitted or prohibited during the trial {11d}

Patients will be informed about which medications or additional interventions they may or may not take in this study. This applies to cytostatic drugs which are an inadmissible concomitant medication in this study as well as therapies other than the intervention mentioned and the surgical treatment described, which are also intended to stimulate bone healing (such as shock waves), and are not permitted during the study. Systemic diseases (e.g., diabetes mellitus) and other medications that may have an influence on bone healing (e.g. non-steroidal anti-inflammatory drugs) will be documented. Accompanying physiotherapy and rehabilitation measures before and during the study to improve the function of the affected extremity will be permitted and desired. Surgical revision for persistent non-union without any improvement in routine imaging should be performed at the earliest four months after the index operation or after the start of treatment with LIPUS. This also corresponds to standard treatment without study participation.

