## Discussion

The aim of this G-BA-funded study is to prove that in patients with non-unions, treatment with low-intensity pulsed ultrasound is not inferior to surgical intervention in terms of the fracture healing rate endpoint (non-inferiority question). Despite medical advances, non-unions occur in approximately 2–10% of all fractures and can affect up to 30% if certain risk factors are involved [1, 2]. To date, surgical revision has been the gold standard in the treatment non-union, with the surgical procedure depending on the type of non-union. The disadvantages of surgical intervention are re-hospitalizations associated with the operation as well as possible secondary diseases and side effects such as postoperative infections, anesthetic incidents and embolisms. A possible alternative to surgical revision for non-unions is treatment with LIPUS, although this is currently considered an individual health service and the benefits over surgery have not yet been shown in a comparative study with sufficient certainty of results.

One of the strengths of our study lies in its design. The study will be conducted as an open, controlled and randomized study with 370 patients over 2 years at approximately 20 study sites. Blinding of patients and investigators is not possible due to the nature of the intervention. A possible bias will be significantly attenuated by the choice of an endpoint committee. To assess the primary endpoint (assessment of fracture healing), only the last available X-ray/CT image of the individual patients will be presented to the independent endpoint committee. This means that the assessor will not be able to draw any conclusions as to whether, for example, implants have been replaced, i.e. whether a surgery has taken place.

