To improve the accuracy and reliability of the study, a approved and CE-marked ultrasound device will be used, which has been used for the treatment of non-unions for several years. Furthermore, the device allows compliance control in the implementation of the treatment for the individual patients. In addition, the SF-12, DASH and LEFS questionnaires are widely used and validated. If non-inferiority of LIPUS compared to standard therapy (surgical revision) is proven in this study, patients with non-unions will have a choice of both invasive and non-invasive/non-surgical therapy methods in the future. The costs for LIPUS treatment should also be covered by health insurance companies in the future if non-inferiority is proven. This would be particularly beneficial for patients with other pre-existing conditions and with an increased risk of anesthesia, as well as for patients who refuse surgery for other reasons.

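### Additional surgery is the only rescue classed as failure for the primary endpoint, so a control who heals after taking up LIPUS would count as a surgical success

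*Protocol article*

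**What the plan says.** All references are to the protocol article.

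- **Rescue offer.** Section {11b} says that, if imaging shows no sign of healing at 120 days, "alternative treatment methods, including a new surgical revision, will be offered"; waiting is also possible. Section {20c} repeats the offer for treatment classed as unsuccessful at visit 3: "the corresponding patients from both treatment groups will be offered alternative or further treatments, including (renewed) surgery". In both places surgery is one option among others.
- **Failure rule.** For the primary endpoint, {20c} states that "all patients who will receive an additional surgical intervention are therefore classified as failures", and gives the reason: "as it can be assumed that the intervention was performed due to a lack of success".
- **Concomitant care.** Section {11d} prohibits "therapies other than the intervention mentioned and the surgical treatment described, which are also intended to stimulate bone healing (such as shock waves" being its example). The exemption for LIPUS and the study surgery is not tied to the arm to which the patient was allocated.
- **Access to the device.** Section {13} says "Patients receiving LIPUS treatment are prescribed an ultrasound device". The Discussion says of LIPUS that "this is currently considered an individual health service", and on payment: "The costs for LIPUS treatment should also be covered by health insurance companies in the future if non-inferiority is proven".
- **Endpoint and population.** Section {12} requires both bony consolidation and functional recovery at 12 months. The primary analysis is by intention to treat ({20c}).

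**The concern.** The reason given for the failure rule is that a rescue shows that the allocated treatment did not work. It applies equally to a control who turns to LIPUS after unsuccessful surgery, but the rule names only surgery. Section {20c} considers several ways in which rescue surgery could distort the comparison and none in which rescue LIPUS could.

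The two directions of crossover are thus handled differently. LIPUS followed by surgery is a failure. Surgery followed by LIPUS, with healing at 12 months, is a success credited to surgery. The surgical healing rate could then contain successes of the competing treatment. At stake are the meaning of that rate and a little power.

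**Working it through.** **1. Can the case arise under the text?**

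| Step | Section | Result for a control with no healing at day 120 |
|---|---|---|
| Rescue offered | {11b}, {20c} | Alternatives beyond surgery are possible |
| Is LIPUS barred? | {11d} | No: LIPUS is exempt, with no mention of arm |
| Is there time? | {11a}, {12} | 365 − 120 = 245 days, longer than a 200-day course |
| Classed as failure? | {20c} | No, unless surgery is repeated |
| Primary endpoint | {12} | Success if consolidation and function are met at 12 months |

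Under intention to treat, that success belongs to the surgical arm.

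**2. The plan's own figure.** Inputs from Sample size {14}: control rate 0.86, LIPUS rate 0.75, margin 0.25, one-sided alpha 0.025, power 90%, Z-test with unpooled variances.

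n = (z₀.₉₇₅ + z₀.₉₀)² × [0.86×0.14 + 0.75×0.25] / (0.25 − 0.11)² = 10.507 × 0.3079 / 0.0196 = 165.06, rounded up to **166** per group, as stated.

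Power at 166 per group: SE = √(0.3079/166) = 0.04307; (0.25 − 0.11)/0.04307 − 1.960 = 1.291; power = **90.2%**.

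**3. Effect of rescue LIPUS in controls.** Expected control failures: 0.14 × 166 = 23.2. Let r be the share of these who take LIPUS without repeat surgery, and h the share of those who meet the endpoint at 12 months. Then

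control rate = 0.86 + 0.14 × r × h.

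The article gives neither r nor h; the values below are assumptions. The LIPUS rate stays at 0.75.

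| r (patients of 166) | h | Control rate | Rise (points) | Power |
|---|---|---|---|---|
| 5% (1.2) | 40% | 86.28% | 0.28 | 89.2% |
| 5% (1.2) | 75% | 86.53% | 0.53 | 88.3% |
| 10% (2.3) | 40% | 86.56% | 0.56 | 88.1% |
| 10% (2.3) | 75% | 87.05% | 1.05 | 86.1% |

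Last row in full: 0.86 + 0.14×0.10×0.75 = 0.8705; difference 0.1205; SE = √((0.8705×0.1295 + 0.1875)/166) = 0.04253; (0.25 − 0.1205)/0.04253 − 1.960 = 1.085; power 86.1%.

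**4. Direction.** A higher control rate moves LIPUS minus surgery towards −25 points, which makes non-inferiority harder to show.

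**5. With rescue LIPUS counted as failure**, the control rate stays at the planned 86% and power at about 90%.

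**The case against.** The strongest reply is that the pathway is inferred. No section says that failed controls are offered LIPUS. The options named are renewed surgery and, in {11b}, waiting. The device is prescribed to the LIPUS group, and outside that group LIPUS is an individual health service. In a two-arm trial the exemption in {11d} was probably meant to cover each patient's allocated treatment, which would make LIPUS in a control a protocol deviation. All of this stands as a reason to expect few cases. It does not settle how a case is classified if one occurs, because the text neither bars it nor calls it a failure.

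A second reply is that the rule covers all patients with additional surgery in both arms, and that leaving an off-protocol crossover in its allocated arm is an accepted intention-to-treat default. That would be a fair choice if the plan left every rescue alone. It does not: it already treats rescue as failure, for a reason that fits rescue LIPUS just as well.

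Third, {20c} advises caution with visit 4 and 5 data after additional interventions, a per-protocol analysis is planned, and further detail is left to the statistical analysis plan. The caution does not change the stated rule. The per-protocol analysis is only a sensitivity analysis, and the article does not say that it removes such patients. The failure rule itself is already fixed here.

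**Conclusion.** The point holds and is minor. Additional surgery is the only rescue event classed as failure, and the rule's own rationale reaches further than its wording. Under the assumed uptake of 5% to 10% of failed controls and healing in 40% to 75% of these, the control rate rises by 0.3 to 1.1 points and power falls from 90% to between 89% and 86%. The offer in {11b} is made only where there is no sign of healing at all, so the true effect may be smaller.

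Four stronger readings are not supported:

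- *Only surgery makes a patient a failure.* Patients who miss the {12} criteria at 12 months also fail.
- *The gap helps LIPUS pass.* It works against LIPUS and cannot create a false non-inferiority claim.
- *The power loss is serious.* Power would fall to about 78% if a quarter of failed controls took LIPUS and 75% of them healed (control rate 0.86 + 0.14×0.25×0.75 = 88.6%), but nothing in the article suggests such uptake.
- *The protocol sends failed controls to LIPUS.* It leaves this open and does not name it.

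**What to change.** In {20c}, extend the primary-endpoint rule so that failure covers (a) any additional surgery for the non-union in either arm and (b) any LIPUS given to a control after unsuccessful surgery. State that continued LIPUS in the LIPUS arm remains allocated treatment and is not a rescue.

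A ban on LIPUS in controls is not needed. It would narrow the alternatives that {11b} promises after failed surgery. Rescue LIPUS can stay available and simply count as failure.

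Cost: one wording change, with no extra patients or visits. A few controls become failures, and off-arm LIPUS use must be recorded in the eCRF. Because the change can only lower the control rate relative to the current wording, it should be made before outcome data are seen.
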